##### Selection of participants

The study population is approximately 82,000 children and pregnant women enrolled in Medicaid and living in the 14 counties. The inclusion criteria are as follows:Children younger than 21 years of age and women who are pregnant or up to 2 months postpartum.Enrollment in Medicaid and assigned to receive dental care from ADS.Home address is located in the selected counties.

The age distribution of the children is as follows: 0 to 5 years old, 36 %; 6 to 15 years old, 46 %; and 16 to 20 years old, 17 %. Twenty-one percent of the children and 11 % of the pregnant women are Hispanic, 5 % of children and 4 % of the pregnant women are from other minority races/ethnicities. All pregnant women, new mothers and children <21 years old are enrolled in Medicaid and the Children’s Health Insurance Program.

Recruitment: Participants are identified through a search of the ADS enrollment database. A random subsample of participants is recruited by telephone to participate in an evaluation of the services by completing a telephone survey. Passive informed consent for caries detection and risk assessment at community settings are obtained, as well as active informed consent for treatments provided at these settings.

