#### PREDICT - the program

In the seven test counties, Expanded Practice Permit Dental Hygienists (EPPDH) will obtain the consent for treatment at community settings and provide selected primary dental services in non-traditional settings and refer patients to primary care dentists and specialists for complex treatments. Community liaisons and case managers, serving as patient navigators, will help the EPPDH obtain the consents and assure that needed treatments are completed at community and dental office settings. This new delivery system is supported by a financial incentive system for high performance (pay-for-performance, capitation payment and global budget) and by an efficient information system for performance monitoring. The service delivery and payment changes focus on the following: 1) identifying Medicaid-eligible children, pregnant women and new mothers and gaining caregiver consent for services in community settings (for example, schools, Head Start, and WIC Centers); 2) providing risk-based preventive and caries stabilization services efficiently at these settings; 3) providing seamless, effective curative care in dental clinics; and 4) incentivizing local delivery teams to meet performance benchmarks.

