### Study measures and data collection

The primary and secondary study measures for impact and process outcomes are presented in Table 1.

**Table 1 Tab1:** PREDICT study measures: impact and process outcomes

Type of outcome	Outcome measures	Description	Operationalization
Impact: primary	Oral health	Proportion of children with untreated dental caries	Number of Medicaid ADS-assigned children with untreated caries divided by the number of children enrolled in Medicaid and assigned to ADS.
Impact: secondary	Patient/consumer satisfaction	Mean quality of care	Mean score for the ratings of quality of care from the parent survey
Process: primary	Dental care utilization by children	Percentage of children who received a dental service	Number of Medicaid-enrolled ADS-assigned children who received a dental service (any CDT code) divided by the number of Medicaid-enrolled ADS-assigned.
Process: primary	Consent for treatment at community settings	Proportion of children for whom consent is obtained	Number of Medicaid ADS-assigned children for whom consent is obtained divided by the number of Medicaid ADS-assigned children.
Process: primary	Oral health screening and risk assessment	Proportion of children who received screening and risk assessment	Number of Medicaid-enrolled ADS-assigned children who received both a screening (CDT 0191) and a risk assessment (CDT 0601-D0603) divided by the number of Medicaid-enrolled ADS-assigned children.
Process: primary	Timely need-based curative treatments	Proportion of children referred for dentist treatment who receive care within 60 days of screening	Number of Medicaid-enrolled ADS-assigned children with dentist treatment needs who visited the dentist (CDT D1000 to D9999) within 60 days of screening divided by the number of Medicaid-enrolled ADS-assigned children with dentist treatment needs.
Process: primary	Dental care utilization by pregnant women and new mothers	Percentage of pregnant women and new mothers who received a dental service	Number of Medicaid-enrolled ADS-assigned pregnant women who received a dental service (any CDT code) divided by the number of Medicaid-enrolled ADS-assigned pregnant women and new mothers.

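### The primary process outcome for women leaves new mothers out of the numerator but keeps them in the denominator, contradicting its own name and description

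*Protocol article*

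**What the plan says.** Table 1 of the protocol article (Study measures and data collection) lists the outcome as "Process: primary Dental care utilization by pregnant women and new mothers". The description column gives it as "Percentage of pregnant women and new mothers who received a dental service". The operationalization column then sets the formula, for women in Medicaid who are assigned to ADS, as "pregnant women who received a dental service (any CDT code) divided by the number of Medicaid-enrolled ADS-assigned pregnant women and new mothers".

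New mothers are a group that the trial means to cover. Under Selection of participants, eligible women are "women who are pregnant or up to 2 months postpartum". The section PREDICT - the program gives the first focus of the intervention as "identifying Medicaid-eligible children, pregnant women and new mothers", and the main research question also names new mothers.

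Nothing elsewhere in the article explains or corrects the formula.

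**The concern.** Within one table row, the name, the description and the denominator cover two groups of women and the numerator covers one. A programmer who follows the operationalization column as written would drop every woman whose only service came in the two months after delivery, yet keep her in the denominator.

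This is the only primary outcome in women: the primary impact outcome and the other four primary process outcomes concern children. What the trial concludes about women's access to care therefore rests mainly on this row. The error would also be silent. The reduced numerator is still a subset of the denominator, so the planned multilevel binomial regression would run without any warning.

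**Working it through.** The article gives no utilization rate, effect size or share of new mothers for women, so there is no stated figure to reproduce. What follows is algebra, then an illustration under labelled assumptions.

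**General form.** Let *u* be the share of all women in the denominator whose only service in the measurement period came postpartum.

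- Rate as described = share of women with any service.
- Rate as written = rate as described − *u*.
- Between-arm difference as written = difference as described − (*u* in test − *u* in control).

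**One status per woman.** Suppose each woman is either pregnant or a new mother when measured. Let *w* be the share who are new mothers, equal in both arms, and let *p*P and *p*N be the utilization rates in pregnant women and new mothers.

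- As described: (1 − *w*)·*p*P + *w*·*p*N
- As written: (1 − *w*)·*p*P
- Shortfall in each arm: *w*·*p*N
- Loss in the between-arm difference: *w* × (effect in new mothers)

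**Assumed range for *w*.** With steady enrolment, 5 to 9 months of Medicaid cover in pregnancy and 2 months postpartum:

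- 9 months: *w* = 2/(9 + 2) = 0.18
- 5 months: *w* = 2/(5 + 2) = 0.29

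Only the 2 postpartum months come from the article (Selection of participants). The months of cover in pregnancy are assumed.

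**Results with equal rates and equal effects in both groups of women.**

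| | *w* = 2/11 | *w* = 2/7 |
|---|---|---|
| True utilization of 40% is recorded as | 0.40 × 9/11 = 32.7% | 0.40 × 5/7 = 28.6% |
| True 20-point gain is recorded as | 20 × 9/11 = 16.4 points | 20 × 5/7 = 14.3 points |

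**Dependence on the effect in new mothers.** Take *w* = 2/11 and a 15-point effect in pregnant women. The written formula always gives 15 × 9/11 = 12.3 points. The described measure gives:

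| Effect in new mothers | Described difference | Written difference |
|---|---|---|
| +15 points | 15.0 | 12.3 |
| 0 | 12.3 | 12.3 |
| −5 points | 12.3 − 0.9 = 11.4 | 12.3 |

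**Dependence on the effect scale.** For true rates of 30% and 45% in both groups of women, at *w* = 2/11, the odds ratio falls from 1.91 to 1.79. The risk ratio stays at 1.50, because the factor (1 − *w*) cancels.

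**Use counted over a period.** If the period includes pregnancy, a woman treated both before and after delivery is in the numerator even under the literal text. Only women with no service while pregnant contribute to *u*, so the loss is smaller than in the one-status illustration.

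**The case against.** The strongest reply is that this is shorthand. The article often writes of pregnant women when it means all eligible women: the abstract and Selection of participants describe the study population that way, and the Statistical analysis plan section weights by eligible children and pregnant women without naming new mothers. Table 1 is loosely worded elsewhere too; the denominator for children's utilization breaks off without its noun. An analyst might well query both groups.

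That reading is plausible, but it does not dispose of the point. The formula itself names new mothers in its denominator: "divided by the number of Medicaid-enrolled ADS-assigned pregnant women and new mothers". The Emergency Department row of the same table uses the same group above and below the line. If shorthand was meant, the same correction to the text is still needed.

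The reply has more force against stronger inferences that a reader might draw, none of which the document supports:

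- *That PREDICT's effect in women is bound to be understated.* This needs a positive effect in new mothers. That is what the trial hopes for, but with no effect the absolute difference is unbiased, and with a negative effect it is overstated. The link for the binomial model is not stated, and a risk ratio can be unaffected.
- *That all care given to new mothers is scored as non-use, or that the rate cannot reach 100%.* Both need one status per woman at measurement. The article states no measurement window. A woman treated while pregnant and again after delivery would still count.
- *That the rate shifts with the mix of pregnant women and new mothers across counties or periods.* The article gives no such share for any county or period.

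**Conclusion.** The mismatch is real. It is an error in the operational definition of a primary process outcome, not a slip in background text. Applied literally, it lowers recorded utilization in each arm and attenuates the absolute between-arm difference to the extent that PREDICT raises use among women treated only postpartum.

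The size cannot be settled from the document. The fall from 20 points to about 16 to 14 is an illustration that rests on one status per woman, an assumed new-mother share of 18% to 29% that is equal in both arms, and equal effects in both groups of women. Counting use over a period that includes pregnancy would make the loss smaller. Untreated caries in children, the primary impact outcome, is untouched, as are the child process outcomes.

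**What to change.** In the operationalization column of this row, insert *and new mothers (up to 2 months postpartum)* after pregnant women in the numerator, so that it matches the name, the description and the denominator. Add that a woman who is both pregnant and postpartum within the measurement period is counted once in the numerator and once in the denominator.

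The cost is one line of text and the matching change to the data query. No new data collection is needed: the Data collection section takes process outcomes from ADS's information systems, which already hold enrolment and coverage dates. The article reports that outcome metrics were still being refined and that recruitment had not begun, so at that stage the correction could be made before the baseline assessments.

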#### Structure outcomes

Structure outcomes are identified below:*Readiness for change of the organization:* Organizational Readiness for Implementing Change (ORIC) questionnaire [25].*Team work and communication:* TeamSTEPPS questionnaire [26].*Staff and provider satisfaction:* Work conditions, provider reactions, burnout and quality and safety of care assessed by Minimizing Errors/Maximizing Outcomes (MEMO) questionnaire [27].*Employee Retention and Turnover:* Turnover rate for the members of the team.*Productivity:* Number of procedures for the members of the team.*Health Information Technology (HIT):* Ability for providers with HIT to interchange field and clinic data electronically.

#### Economic outcomes

Economic outcomes include the costs for the following:Outreach activities: actual FTE expenditures on community outreach.Oral health screening and caries risk assessment.Preventive treatment.Restorative treatment.Dental care.Total dental: sum of outreach and dental care costs.Outpatient medical.Emergency department visits.Inpatient hospitalizations. Total medical. Outpatient prescriptions. Total cost: Sum of dental, medical, and prescription costs.

Potential confounders or effect modifiers at the county level include the percentage of participants in different age categories, at elevated caries risk, and in different race/ethnicity categories.

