#### Data collection

Data on *impact outcomes* will be obtained through a clinical examination of children and a telephone survey of parents/caregivers and children at baseline and after 24 months. A random sample of Medicaid-enrolled ADS-assigned children will be obtained and stratified by county, at baseline and 24 months post-implementation. The sample will include children whose caregivers either consented or did not consent for care. It will also include children who sought care directly from a dental office. For the survey, staff members will be given a list of enrollees to telephone and move down the list in order until the required sample size is reached. Each individual will be called a minimum of five times. For the clinical examination, staff members will be given a list of enrollees, and they will exam the children in the community settings.

Data on *process and cost outcomes* will be obtained through ADS’s health information systems: Medicaid enrollment database, ADS database (ADIN), electronic dental records and payroll ledger. All Medicaid-enrolled ADS-assigned children population will be included in the process and cost evaluation. Enrollment information including patient identifiers, birth date, gender, race/ ethnicity, coverage dates and assigned primary care provider will be obtained from ADS’s enrollment database and linked to State Medicaid claims. Medicaid claims will be accessed to collect emergency department, medical care and prescription services and costs. Data on *structure outcomes* will be obtained through staff online surveys at baseline and after 24 months and continuously through ADS’s health information systems and internal records. Fidelity information will be obtained through staff surveys and internal records.

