#### Statistical analysis plan

Descriptive statistics (means, standard deviations, counts, and percentages) are calculated for all variables of interest overall and stratified by age group. The primary hypothesis is that the test intervention participants will have lower number of untreated dental caries than the control participants and the absolute changes indicate a reduction in disparities. Multilevel regression are used to assess for changes in the impact and process outcomes between pre- and post-implementation in the test and control counties, weighted by the number of eligible children/pregnant women in the county at each time point and adjusting for within-county correlation between pre- and post-implementation outcomes [30]. We use multilevel linear regression for mean scores and multilevel binomial regression for binary measures. Additional multilevel regression modeling are used to compare changes in the impact and process outcomes by child age category (for example, 0 to 5, 6 to 15 and 16 to 20 years old) or race/ethnicity, adjusting for clustering within county and weighting by number of eligible children in each age or race/ethnicity category.

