#### Economic statistical analysis plan: cost per member per month

The hypotheses are that the new model will increase outreach dental care costs, yet reduce total costs compared with no change in the control model. This is evaluated using a difference in differences approach, adjusting for within cluster variance, to measure the reduction in cost per patient per month for pre versus post intervention effects within the intervention group and for control versus intervention effects. Individual cost components are also evaluated as outcomes in order to elucidate the specific areas of cost which contribute to differences in total costs. Patients in the intervention and control groups are matched using a propensity score based on patient demographics (age, gender, and race), primary medical provider, and primary dental provider. Generalized linear models are constructed using the gamma family with a log-link in order to account for highly skewed cost data. The cost outcomes are the dependent variables while an indicator for the presence of the intervention are the primary independent variable.

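### The main caries model states no individual age or race/ethnicity term, although the examined sample spans ages 0 to 20 and its age mix could shift differently between arms

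*Protocol article*

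**What the plan says.** At the end of the section Economic outcomes, the protocol article states: "Potential confounders or effect modifiers at the county level include the percentage of participants in different age categories, at elevated caries risk"; race/ethnicity categories complete the list. All three are county percentages.

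The section Statistical analysis plan gives the main model for impact and process outcomes: "Multilevel regression are used to assess for changes in the impact and process outcomes between pre- and post-implementation in the test and control counties". Only two further features of that model are named. Counties are weighted by how many eligible people they have in each period, and the model allows for a county's two results being correlated. No age or race/ethnicity term is stated.

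Age and race/ethnicity do appear elsewhere:
- Descriptive statistics "are calculated for all variables of interest overall and stratified by age group".
- "Additional multilevel regression modeling are used to compare changes in the impact and process outcomes by child age category" or race/ethnicity, "weighting by number of eligible children in each age or race/ethnicity category".
- In the cost analysis, patients are matched on a propensity score that includes individual age, gender and race.

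Under Data collection, the sample for the clinical examination is random, stratified by county, and obtained at baseline and at 24 months. Staff examine the listed children in community settings. "Enrollment information including patient identifiers, birth date, gender" and race/ethnicity come from the enrollment database. Process and cost outcomes use the whole enrolled population of children.

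**The concern.** Untreated caries is likely to differ between infants, schoolchildren and young adults, and the primary outcome pools them all. The sample is not stratified by age, so the mix of those actually examined is left to the list and to who can be reached.

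Reach may not be the same in both arms. PREDICT expands work in schools, Head Start and WIC centers in test counties (PREDICT - the program), while control counties have preventive care at some community settings only (Control group). If examined children in test counties become younger or older between baseline and 24 months, and those in control counties do not, part of the apparent change in caries is a change in age. Randomizing counties and drawing a random list do not prevent this. Weighting by the eligible number in a county does not restore the age mix within it.

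County percentages are a poor tool here. They describe the county, not the children examined, and they use up county-level degrees of freedom. Individual covariates do not have that cost.

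**Working it through.** **1. The plan's own power figure (Sample size).** Inputs: 7 v 7 counties, 80 children per county, ICC 0.05, 25% v 10%. Two-sided 0.05 is stated for satisfaction and assumed here.
- Design effect = 1 + (80 − 1) × 0.05 = 4.95.
- Effective n per arm = 7 × 80 / 4.95 = 113.1.
- SE = √[(0.25 × 0.75 + 0.10 × 0.90) / 113.1] = √(0.2775 / 113.1) = 0.0495, or 5.0 points.
- Power: 79.4% (noncentral t, 12 df), 80.1% (normal, one cluster fewer per arm), 80.3% (continuity-corrected). The stated 80% is reproduced, with no age adjustment in it.

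**2. County percentages as covariates.** Three age categories need 2 terms, three race/ethnicity groups (Hispanic, other minority, remainder) need 2, and caries risk needs 1. With 14 − 2 = 12 df between counties, 12 − 5 = 7 would remain.

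**3. Assumed age-specific prevalence.** The documents give none; their 25% refers to ages 6 to 10 only. Two extremes are used for ages 0-5 / 6-15 / 16-20: 20/25/25% (shallow) and 5/30/35% (steep). The age mix is 36/46/17% (Selection of participants), rescaled from 99% to 100%.

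**4. Chance imbalance in the sampled age mix.** Let V be the between-age variance of prevalence, with 560 children per arm and time point.

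| | Shallow | Steep |
|---|---|---|
| Overall prevalence | 23.2% | 21.8% |
| V | 0.00058 | 0.01638 |
| SD of test-control difference, √(2V/560) | 0.14 points | 0.77 points |
| SD of difference in change, √(4V/560) | 0.20 points | 1.08 points |

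**5. Systematic shift from ages 0-5 to 6-15.** Movement = shift × (prevalence at 6-15 − prevalence at 0-5). A shift the other way changes the sign.

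| Shift | Shallow | Steep |
|---|---|---|
| 10 points | 0.10 × 5 = 0.5 points | 0.10 × 25 = 2.5 points |
| 20 points | 0.20 × 5 = 1.0 point | 0.20 × 25 = 5.0 points |

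Against the SE of 5.0 points in step 1, a 10-point shift is 0.1 to 0.5 SE and a 20-point shift is 0.2 to 1.0 SE. If the shift occurs in one arm and one period only, all of it enters the difference in change.

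**6. Precision.** Age explains V / [p(1 − p)] = 0.3% to 9.6% of individual variance. Removing that share of within-county variance takes power (t, 12 df) from 79.4% to between 79.4% and 80.1%.

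**The case against.** The strongest reply is that silence is not exclusion. The article condenses a fuller plan, the SAP is not shown, and a covariate list commonly belongs there. Naming variables as potential confounders or effect modifiers suggests some use, and the models by age and race/ethnicity are one legitimate use. This stands in part: nothing shows that the trial will refuse to adjust. But the article does set out what its main model adjusts for, and it gives individual age control to costs and states none for the primary outcome. Comparing changes by age category examines effect modification; it does not adjust the overall contrast.

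A second reply is that counties are randomized and children randomly sampled, so the unadjusted comparison is valid and adjustment is a matter of taste. That holds for chance imbalance, which is small. It does not cover differences in who is reached for examination.

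Four stronger inferences are tempting, and the documents do not support them:
- That every planned model leaves out age and race/ethnicity. The additional multilevel models and the cost matching use them.
- That process outcomes share the sampling problem. They cover the whole enrolled population.
- That the caries result is already shown to be biased. No document reports an age shift; the shifts above are assumed.
- That the plan would adjust for a post-implementation caries-risk value. It does not say so. It leaves the time of measurement open, and risk assessment is itself a process outcome that PREDICT aims to increase.

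**Conclusion.** The point holds for the primary caries comparison. As written, it has no individual age or race/ethnicity adjustment, and the named confounders are in a form that 14 counties can hardly support. The potential distortion is about 0.5 to 2.5 percentage points for a 10-point age shift and 1 to 5 points for a 20-point shift, against a 15-point target. That is modest, but sampling more children would not reduce it. Chance imbalance (SD up to about 1.1 points on a difference in change) and power (a gain of less than 1 point) would not by themselves justify the change.

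The sizes rest on assumed prevalences and assumed shifts. They also take the two examination samples as separate draws, which is the natural reading of Data collection but is not stated in so many words.

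**What to change.** In the article's section Statistical analysis plan, state that the primary caries model includes individual age category (0-5, 6-15, 16-20) and race/ethnicity from the enrollment file as fixed effects, or that results are standardized to the enrolled age mix. Report the marginal risk difference in either case. The planned age-category models and their eligible counts supply most of what standardization needs. Extending this to the process models is optional.

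In Economic outcomes, state that if elevated caries risk is used for adjustment, only a pre-implementation value is used.

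The cost is a few sentences and one standardization step; no new data are needed. The limit should be stated too: age and race/ethnicity adjustment does not remove selection on other characteristics of the children who are reached.
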